### Data Analysis

The data will be initially assessed for outliers, missing, and nonsensical variables. These variables will not be imputed, since they will be handled as missing. Similar studies that involved CBT and e-CBT demonstrated a dropout rate of up to 40% for both conditions once the study concluded [49]. Thus, this study will intentionally oversample the experimental and control groups to account for this dropout rate. Considering the effect size for face-to-face RPT reported by Harada et al [50] (2021) for CBI (effect size=0.65), a significance level of α=.05 and a power of 0.90, a sample size of 60 (30 per arm) would be sufficient to detect substantial changes from our interventions [51]. As this is the first study aiming to establish an e-RPT program for AUD, this sample size calculation relies on data from face-to-face RPT and takes into account the established effectiveness of online psychotherapy compared to face-to-face psychotherapy [30].

The analysis will begin by examining the data for missing, nonsensical, and outlying variables. The data will then be analyzed on a per-protocol basis, excluding missing data, and with intention-to-treat analysis to assess the clinical effects of the program on participants who dropped out prematurely. All calculations will be done using a 2-tailed significance level of α=.05, except for when a Bonferroni correction is needed. The demographic information of program completers and program dropouts will be compared using independent sample *t* tests to identify possible differences. A 2 by 3 repeated measures ANOVA of the primary (daily drinking and relapse) and secondary (SCQ-100, Q-LES-Q-SF, RS-14, CBI, and PHQ-9) outcomes will be conducted to test for the effects of the interventions (e-RPT or face-to-face RPT) throughout the 10-week treatment (0, 5, and 10-week assessment points). Linear regression (for continuous outcomes) and binomial regression analysis (for categorical outcomes) will be used to identify variables associated with outcome measures. Additionally, OPTT will collect usage statistics (ie, number of logins per day, amount of time spent logged in) and compare them to face-to-face metrics (ie, attendance to weekly 1-hour face-to-face sessions) to determine cost and time savings between the 2 programs. All statistical analyses will be conducted using IBM SPSS Statistics for Mac (version 24; IBM Corp).

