The strengths of this program and this study include the use of asynchronous psychotherapy through predesigned web-based modules. These web-based modules have been shown to increase therapy efficiency by allowing a web-based therapist to deliver care to 3 to 4 patients at a time compared to 1 synchronous session [30,39,40]. The use of a web-based platform like OPTT allows for the automatic and reliable collection of user analytics, which can then be used to continuously improve and optimize the delivery of web-based psychotherapy programs. Given that face-to-face RPT has been previously validated in the literature, this study hypothesizes that e-RPT will be effective at maintaining abstinence, reducing the risk of relapse and depression symptomatology, and improving quality of life, resiliency, and coping behaviors [12,24,31,32,50]. Furthermore, comparing our proposed e-RPT program to a validated face-to-face therapeutic approach (RPT) strengthens the design of this RCT and the conclusions that will stem from this evidence.

Despite the strengths of this program, the web-based mode of delivery of this program may have some potential limitations. The main limitation is that participation requires a reliable internet connection and sufficient technology literacy. This limitation could introduce biases in participant demographic characteristics. Thus, this study will analyze demographic factors through multiple sample *t* tests to determine if these factors could impact treatment outcomes. Additionally, due to the delivery mode and design of the program, it is not possible to conceal client allocation. Moreover, web-based psychotherapy is often characterized by a dropout rate of up to 40% by the end of the treatment [49,50]. To account for this without compromising statistical power, this study is intentionally oversampled.

The knowledge dissemination plan for this study includes publishing the outcomes of this study in a peer-reviewed, academic journal. The research team will also attend academic meetings and conferences to present these findings and commit to continuing education in the relevant research areas. Furthermore, the dissemination and application of knowledge will be further enhanced through the collaboration of the Canadian enterprise, OPTT Inc. Additionally, by providing this service to clinicians, the care capacity for accessible, affordable, and high-quality mental health care could be more rapidly scaled across Canada.

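### The intention-to-treat analysis is meant to cover dropouts, but no imputation plus a repeated measures ANOVA removes everyone with a missing week 5 or week 10 assessment

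*Protocol article*

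**What the plan says.** Three statements in the protocol article, Methods, Data Analysis, bear on this point.

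- **Missing values.** After a sentence that lists outlying, missing and nonsensical variables together, the plan says: "These variables will not be imputed, since they will be handled as missing".
- **Model.** The test of the interventions is "A 2 by 3 repeated measures ANOVA of the primary (daily drinking and relapse) and secondary" outcomes, at the "0, 5, and 10-week assessment points". The software is SPSS version 24.
- **Analysis sets.** Two are planned: "analyzed on a per-protocol basis, excluding missing data, and with intention-to-treat analysis to assess the clinical effects of the program on participants who dropped out".

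Data Analysis cites dropout of up to 40% in both conditions in similar studies. The Discussion gives the timing: "web-based psychotherapy is often characterized by a dropout rate of up to 40% by the end of the treatment". The response in both places is to oversample. Linear and binomial regression also appear. The Abstract (Results) gives them as the way outcome data will be assessed, while Data Analysis gives them the narrower job of finding variables associated with the outcomes.

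**The concern.** The intention-to-treat analysis has one stated purpose, which is to say something about people who dropped out. The stated method removes most of the people it is meant to describe, because a repeated measures ANOVA needs a complete set of visits and nothing is filled in. For anyone with a missing assessment, the two planned analyses then use the same exclusions.

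The primary outcomes are drinking and relapse. It is plausible, though the documents do not measure it, that people who relapse are also those who stop attending or stop completing assessments. An analysis of those who remain is no longer protected by randomisation. Relapse would tend to look rarer than it is, and the comparison of arms would depend on who left each arm. The hypothesis is that the two programs have similar effectiveness, so readers will want to know that any similarity or difference is not a product of dropout.

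**Working it through.** **1. Do the three statements fit together?** Take a participant who leaves in week 7 and gives no week-10 assessment.

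- Per-protocol: excluded, because missing data are excluded.
- Intention-to-treat: the week-10 value is not imputed, and the repeated measures ANOVA drops the case for lack of one of three values. Excluded.
- Regression on the week-10 outcome: there is no observed value, so excluded.

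The protocol states no mixed model, carry-forward rule or rule counting missing as relapsed that would bring this person back. A participant who stops the modules but completes weeks 5 and 10 stays in the intention-to-treat set. The protocol does not say whether people who stop will still be assessed.

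**2. How many are left?** Inputs: 60 randomised, 30 per arm, dropout up to 40% (all from the protocol). It is assumed that each dropout misses at least one assessment.

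Analysed = 60 × (1 − dropout).

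| Dropout | Analysed | Per arm |
|---|---|---|
| 10% | 54 | 27 |
| 20% | 48 | 24 |
| 30% | 42 | 21 |
| 40% | 36 | 18 |

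At 40%, 24 randomised participants are lost. The standard error relative to no dropout is √(30/18) = 1.29. If the planning effect size of 0.65 is read as a between-arm difference (two-sample t test, two-sided 0.05), power is 0.70 at 30 per arm and 0.47 at 18 per arm. The plan's own total of 60 for power 0.90 is not reproduced on that reading, which needs 51 per arm. That is a separate matter, and this point does not depend on it.

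**3. What can selection do to relapse?** The rates here are assumed for illustration; the documents give none.

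- *Understatement.* Completers relapse at 50% and dropouts at 80%, with 40% dropout. True rate = 0.6 × 0.50 + 0.4 × 0.80 = 0.62. The completer analysis reports 0.50.
- *A difference hidden.* Same rates, dropout 40% in one arm and 20% in the other. True rates are 0.62 and 0.8 × 0.50 + 0.2 × 0.80 = 0.56. Completers show 0.50 and 0.50.
- *A difference created.* True rate 0.56 in both arms, dropouts relapse at 80%, dropout 40% and 20%. Completer rates are (0.56 − 0.4 × 0.80)/0.6 = 0.40 and (0.56 − 0.2 × 0.80)/0.8 = 0.50.

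**4. The same for a continuous score.** Assumptions: no true difference, unit variance, correlation 0.6 between adjacent visits, and dropout when the week-5 score (higher is worse) plus unit-variance noise exceeds a cut-off that gives dropout rate r. The completers' mean at week 10 is then −(0.6/√2) × φ(z)/(1 − r), where z is the normal quantile at 1 − r.

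- r = 40%: −0.424 × 0.644 = −0.273
- r = 20%: −0.424 × 0.350 = −0.148
- r = 10%: −0.424 × 0.195 = −0.083

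The arm with more dropout looks better by 0.12 SD at 40% v 20% and by 0.19 SD at 40% v 10%. At 40% v 40% the bias is 0.00. A simulation under the same assumptions gave 0.12, 0.19 and 0.00.

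**The case against.** Several counter-arguments have force.

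**Regression as the outcome model.** The Abstract names linear and binomial regression for the outcome data, so the ANOVA may not be the only test. A binomial regression of relapse needs one outcome per person, and a relapse recorded in the diary before dropout could count. This stands in part. But Data Analysis confines regression to associated variables, and regression too uses observed values only. Someone who leaves without a recorded relapse still has no week-10 status.

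**The no-imputation sentence as a cleaning rule.** Its stated reason fits outlying and nonsensical values better than missing ones, and the exclusion of missing data is attached only to the per-protocol analysis. That may be the intention. As written, the sentence covers missing values, and the ANOVA would drop the incomplete cases even without it.

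**Detail left to an analysis plan.** This is fair for naming the primary set and for defining per-protocol by adherence, so neither is counted here as a fault. It does not cover a stated method that defeats its stated purpose.

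**Stronger readings that the documents do not support.**

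- A reader might infer that no dropout can enter the intention-to-treat analysis, or that the two sets are identical. That holds only for those with a missing assessment.
- A reader might infer that 40% will be lost. The protocol says up to 40%, so 36 of 60 is the upper planned loss from dropout.
- A reader might infer that the bias favours the hypothesised similarity. The examples show that selective dropout can create a difference as easily as hide one. With equal dropout of 40%, which is how the protocol describes both conditions, the between-arm bias in the continuous example is zero, although relapse is still understated in the relapse example.

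**Conclusion.** The contradiction is real and lies within the Data Analysis section. Followed as written, participants without a week 5 or week 10 assessment leave both analyses, so the intention-to-treat analysis cannot do what it is included for in their case. At the protocol's upper dropout figure, about 24 of 60 randomised participants would be absent from the primary result, if dropouts are not assessed after leaving.

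The understatement of relapse rests on the plausible but unmeasured assumption that dropouts relapse more often than completers. Bias between arms needs dropout to differ between arms in amount or in its reasons, and its direction cannot be predicted. Oversampling can at most protect precision, and comparing the demographics of completers and dropouts by t tests can flag some imbalance but corrects none. The factor of 1.29 is measured against no dropout at all, so no analysis method would recover the whole of it.

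**What to change.** - Name the analysis of all randomised participants, as randomised, as primary, and keep per-protocol as supportive.
- Replace the repeated measures ANOVA for continuous outcomes by a likelihood-based mixed model (SPSS MIXED, available in version 24) that uses every observed visit. Keep baseline in the outcome vector, constrained to be equal between arms, and take the week-10 arm difference as the contrast. With baseline only as a covariate, anyone who leaves before week 5 would still be lost.
- Analyse relapse as a binary outcome, using all diary data up to dropout with multiple imputation. Add a sensitivity analysis that counts dropouts as relapsed.
- Limit the no-imputation sentence to outlying and nonsensical values.

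The cost is a revision of the analysis wording and a little more programming in the same software, with no new data. The main analysis then assumes that data are missing at random given what was observed, and the sensitivity analysis probes that assumption. Participants with only a baseline value will add little direct information about the arm difference, so the gain is mainly in using partial data and in keeping the randomised comparison intact.

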**Objective:**

This study protocol aims to establish the first academic e-RPT program to address AUD in the general population. The primary objective of this study is to compare the efficacy of e-RPT to face-to-face RPT in decreasing relapse rates. The secondary objective is to assess the effects of e-RPT on quality of life, self-efficacy, resilience, and depressive symptomatology. The tertiary objective is to evaluate the cost-effectiveness of e-RPT compared to face-to-face RPT.

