Participant inclusion criteria are being 18 years or older at the start of the study and having a diagnosis of mild to moderate AUD according to the MINI (2 to 5 MINI AUD symptom criteria) [20], competence to consent and participation, ability to speak and read English, and consistent and reliable access to the internet. Additionally, contemplation about stopping or having stopped consuming alcohol in the past 30 days is required. This will be assessed by the RCQ (participants should be in the contemplation or action stage according to the questionnaire) and by asking them about when they stopped drinking or began considering alcohol cessation [34,35]. Exclusion criteria are acute hypomanic or manic episodes, acute psychosis, other active substance use disorders classified as moderate or severe, active suicidal or homicidal ideation, untreated clinically substantial somatic symptoms or mental disorders, or current enrollment in another relapse prevention program. Additionally, men who consumed more than 4 drinks per day or 14 drinks per week and women who drank 3 drinks per day or 7 drinks per week in the past month will be excluded [36].

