### Outcome Measures

The primary objective of this study will be to determine if e-RPT has similar effectiveness to face-to-face RPT at reducing alcohol consumption and preventing relapses. This study defines relapse as either the consumption of at least 2.5 oz. of pure ethanol, which is around 4 and a half standard drinks (Canadian guidelines for standard drinks: 12 oz of beer with 5% ethanol, 12 oz of cider with 5% ethanol, 5 oz of wine with 12% ethanol, and 1.5 oz of spirits with 40% ethanol) [41,42] on one occasion or hospitalization because of alcohol drinking [43]. Therefore, to determine the effectiveness of this program, daily alcohol consumption will be recorded in a drinking diary accessible through OPTT. This diary will ask the participants to report how many drinks they consumed on each day of the week, where they had those drinks, with whom, and if their alcohol consumption resulted in hospitalization (Figure 1).

The study will also determine whether e-RPT and face-to-face RPT have a beneficial effect on self-efficacy, quality of life, resiliency, coping behaviors, and depressive symptomatology. These metrics will be assessed through the following scales: Situational Confidence Questionnaire (SCQ-100) [44], 14-item Resilience Scale (RS-14) [45], Coping Behaviors Inventory (CBI) [46], Patient Health Questionnaire (PHQ-9) [47], and Quality of Life Enjoyment and Satisfaction Questionnaire—Short Form (Q-LES-Q-SF) [48]. These assessment scales will be completed at study entry (baseline), amid the program (week 5), and post treatment (week 10). After the treatment period, we will conduct follow-up assessments with all our outcome measures at 3, 6, and 12 months. The amount of time that e-RPT therapists spend writing feedback compared to the 1-hour face-to-face session will be used as a measure of therapists’ time efficiency and will be tracked on the OPTT platform.

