## Results

According to the literature on the efficacy of face-to-face psychotherapy compared to web-based psychotherapy in the management of AUD, we hypothesize that both e-RPT and face-to-face RPT will reduce alcohol consumption and relapse risk and improve secondary outcome measures (depressive symptomatology, self-efficacy, quality of life, and resilience) [44-47]. Recruitment and data collection are expected to end in October 2023. Data analysis will be concluded by December 2023, at which point the process of knowledge dissemination will begin, including but not limited to peer-reviewed publications, scientific presentations, grant proposals, and reports.

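### Relapse, an event, is put into a repeated measures ANOVA with a week-0 point that eligibility probably holds near zero; the model suits it poorly and could not then show the hypothesised fall

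*Protocol article*

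**What the plan says.** **Model.** Data Analysis specifies "A 2 by 3 repeated measures ANOVA of the primary (daily drinking and relapse) and secondary" outcomes, "throughout the 10-week treatment (0, 5, and 10-week assessment points"). The same section uses binomial regression only to look for variables associated with the outcomes. The Results paragraph of the abstract instead assigns binomial regression to categorical outcomes in general.

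**Outcome.** Outcome Measures defines relapse as "consumption of at least 2.5 oz. of pure ethanol, which is around 4 and a half standard drinks". After a list of drink sizes, the definition goes on: "on one occasion or hospitalization because of alcohol drinking". The data come from a daily drinking diary kept on the study platform.

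**Eligibility.** Study Design and Participants excludes "men who consumed more than 4 drinks per day or 14 drinks per week and women who drank 3 drinks per day or 7" weekly, judged over the month before entry. The intake questions in Textbox 1 ask for the average number of drinks on drinking occasions, not the largest number.

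**Objective.** The abstract states: "The primary objective of this study is to compare the efficacy of e-RPT to face-to-face RPT in decreasing relapse rates". The Introduction gives the same objective but adds alcohol consumption in its hypothesis. Outcome Measures puts both consumption and relapse in the primary objective. The Results section expects that "both e-RPT and face-to-face RPT will reduce alcohol consumption and relapse risk".

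**The concern.** Repeated measures ANOVA is a model for a continuous outcome with comparable variance across time points. Relapse as defined here either happens in a period or does not. The first of the three time points also falls where the entry criteria appear to rule out the consumption part of the definition. An outcome fixed at zero at week 0 has no variance there and can only rise, whereas the article expects relapse risk to fall. At stake are the size and clarity of the primary treatment estimate, some power in a trial of 60, and a time effect that would show relapse rising in both arms for reasons of design.

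**Working it through.** **1. Ethanol per drink (Outcome Measures).** Beer and cider: 12 oz × 5% = 0.6 oz. Wine: 5 oz × 12% = 0.6 oz. Spirits: 1.5 oz × 40% = 0.6 oz.

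**2. The stated threshold.** 2.5 / 0.6 = 4.17 drinks. The article's approximation, "consumption of at least 2.5 oz. of pure ethanol, which is around 4 and a half standard drinks", is not reproduced: 4.5 × 0.6 = 2.7 oz.

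**3. Caps against threshold.** Men: at most 4 drinks, 4 × 0.6 = 2.4 oz. Women: fewer than 3 drinks, under 3 × 0.6 = 1.8 oz. Both lie below 2.5 oz. If the caps are daily maxima, nobody eligible can meet the consumption part at week 0, and only hospitalization remains possible.

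**4. Effect on the arm main effect.** With week 0 equal to zero, a participant's mean over the three points is (0 + y5 + y10)/3, which is 2/3 of the on-treatment mean (y5 + y10)/2. The estimated arm difference therefore shrinks by one third. Its standard error shrinks by the same factor, so the p-value of the main effect does not suffer; the reported size does.

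**5. Simulation.** The article gives no relapse rates, so these are assumptions: 20% and 30% relapse at weeks 5 and 10 in one arm, 40% and 60% in the other; week 0 zero for all; latent correlation 0.5 between weeks 5 and 10; relapse scored 0/1; 3,000 runs.

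- True on-treatment mean difference: (0.20 + 0.30)/2 = 0.25. Average estimated main effect: 0.168, close to 0.50/3 = 0.167.
- Average arm contrast in change from week 0 to week 10: 0.30, equal to the true week-10 difference, 0.60 − 0.30.
- Power:

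| Per arm | Arm-by-time test | Two-proportion test at week 10 | Arm main effect |
|---|---|---|---|
| 30 | 0.58 | 0.67 | 0.72 |
| 18 (30 × 0.6, after 40% dropout) | 0.37 | 0.49 | 0.50 |

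- With a smaller difference (30% and 50% in the second arm) and 30 per arm, the three powers are 0.28, 0.38 and 0.35.
- With equal arms (20%/30%, or 10%/15%), type I error of the two ANOVA tests is 0.043 to 0.056 uncorrected. The Greenhouse-Geisser version of the arm-by-time test gives 0.039 to 0.046.

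**The case against.** The strongest reply is that the primary question is between arms, and the ANOVA answers it. That stands. Even with week 0 set to zero for everyone, the arm-by-time contrast recovers the week-10 risk difference and type I error stays close to 5%. A reader might infer that the model cannot estimate the relapse comparison at all; the calculation contradicts this.

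The week-0 floor is also an inference. Intake asks about averages, so a man averaging 4 drinks or fewer may have had one occasion above 4.17. Earlier alcohol-related hospitalization is not an exclusion, and the period covered by the week-0 value is not stated. Near zero is defensible; exactly zero is not.

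Three further readings are tempting but go beyond the text:

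- **Most diary events are discarded.** If only weeks 5 and 10 counted, and a 60% ten-week risk were spread evenly, the weekly risk would be 1 − 0.4^(1/10) = 0.088, and about 1 − 0.912² = 17% would show an event. The article does not say that relapse is a one-week snapshot. Counts, or periods since the previous assessment, are equally possible and would use the whole diary.
- **Two primaries give 9.75% familywise error.** 1 − 0.95² = 0.0975 needs independent tests and no correction. Both outcomes come from one diary, and Data Analysis allows for a Bonferroni correction, though without saying when. Nor is consumption slipped in only at the analysis stage, since Outcome Measures already names it.
- **The relapse threshold has two working values.** The 4.5 is offered as an approximation. With whole-drink entries, 4.17 and 4.5 both mean 5 drinks or more, so classification is the same.

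**Conclusion.** The point holds in limited form. The Data Analysis section fixes an unsuitable model for relapse, and it conflicts with the abstract on whether a categorical outcome goes to ANOVA or to binomial regression. If the drinking caps act as daily maxima, week-0 relapse is at or near zero with almost no variance, and change from week 0 cannot show the reduction expected in the Results section.

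For the arm comparison, the cost is a main effect about one third too small and an arm-by-time test somewhat weaker than a direct week-10 comparison. It is not a loss of estimability or of error control. The power figures depend on assumed rates and 0/1 scoring. The benchmark is a week-10 comparison; power for the any-relapse outcome proposed below was not calculated. The inconsistent primary-outcome wording is a secondary matter, and the drink conversion a minor one.

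**What to change.** 1. Reconcile Data Analysis with the abstract. Define the relapse outcome as any relapse from randomisation to week 10, taken from the full daily diary. Compare arms by binomial or logistic regression adjusted for baseline drinking, and report a risk difference with 95% CI. Leave week 0 out of the relapse model as an outcome; it belongs there only through the baseline covariate. State how participants whose diary stops early are classified.
2. Align the primary outcome across the abstract, Introduction, Outcome Measures and Data Analysis: either relapse alone, or relapse and consumption with the Bonferroni correction stated.
3. Give 2.5 oz as about 4.2 standard drinks.

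The cost is a change of wording and of analysis specification, made before the data are analysed. The diary is already collected, and binomial regression is already named in the article.

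### Daily drinking, a primary diary count, is compared between arms by an unadjusted 2 by 3 repeated measures ANOVA: valid under the null, but inefficient, mainly because baseline drinking is not used as a covariate

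*Protocol article*

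**What the plan says.** The Data Analysis section of the protocol article sets out "A 2 by 3 repeated measures ANOVA of the primary (daily drinking and relapse") and of the secondary scales, over the "0, 5, and 10-week assessment points". Linear and binomial regression follow, but only to find variables associated with the outcomes. The same section fixes the error rate: "All calculations will be done using a 2-tailed significance level of α=.05", apart from any Bonferroni correction.

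Under Outcome Measures, "daily alcohol consumption will be recorded in a drinking diary accessible through OPTT", and participants enter "how many drinks they consumed on each day of the week". The outcome is therefore a non-negative count.

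Two entry rules in Study Design and Participants shape it. First, "contemplation about stopping or having stopped consuming alcohol in the past 30 days is required", so people already at zero join people still drinking. Second, "men who consumed more than 4 drinks per day or 14 drinks per week" are excluded, with a lower limit for women, which caps drinking at entry.

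The article gives no mean, standard deviation, share of zeros or target difference for drinking.

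**The concern.** Repeated measures ANOVA works on the raw scale with an additive arm effect and equal error variance. A drink count from a part-abstinent sample is unlikely to fit that. The entry cap acts only at baseline. The drinking part of the relapse definition is 2.5 oz of ethanol, which the article puts at about four and a half standard drinks, above the daily limit allowed at entry. Follow-up data may therefore combine a mass at zero with values beyond the baseline range.

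The group-by-time test also spends two degrees of freedom on any difference in pattern. It treats week-0 drinking as one more outcome, although that value could explain part of the week-10 variation.

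Precision is at stake. With 40% dropout, 30 x (1 - 0.40) = 18 per arm remain. The hypothesis is similar effectiveness and the article states no margin, so an imprecise comparison tends towards a non-significant result that readers may take as support.

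**Working it through.** **The plan's own figure.** There is none for drinking. The only power statement concerns the CBI: effect 0.65, power 0.90, 30 per arm. As a two-arm comparison it does not reproduce: 2 x (1.960 + 1.282)^2 / 0.65^2 = 49.7, so 50 per arm. That is a separate matter and says nothing about drinking.

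**Inputs.** From the article: 30 per arm, 18 after 40% dropout, two-sided 5%, weeks 0, 5 and 10. Assumed, because the article is silent: the count distribution, the share of zeros, and a halving of the drinking rate as the effect.

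**Step 1: is the planned test valid under the null?** In a three-visit simulation of overdispersed counts (6000 runs per cell), the Greenhouse-Geisser group-by-time test rejected 2.9-4.9% of the time and the uncorrected test 3.7-5.4%. A two-sample t test on one count per person (3000 runs per cell) rejected 4.0-5.6%. Across all checks the range is about 2-6%.

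**Step 2: what does lack of adjustment cost?** Suppose equal variance s^2 at both times and correlation r between baseline and week 10.
- Change from baseline, the contrast inside the group-by-time test, has variance 2s^2(1 - r).
- The baseline-adjusted value has variance s^2(1 - r^2).
- The ratio of adjusted to change is (1 + r)/2: 0.50 at r = 0 and 0.75 at r = 0.5.

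In large samples adjustment is therefore never less precise than change, and it also avoids the two-degree-of-freedom test. In simulation with the rate halved and 18 or 30 per arm, power was about 0.06-0.30 for the planned group-by-time ANOVA and 0.11-0.57 for a baseline-adjusted linear comparison at week 10. These are ranges over scenarios, so their ends need not pair. The three-visit simulation of step 1 gave the planned test 0.10-0.39 at a halved rate. In a further check (4000 runs per cell, 30% or 50% near-abstinent, baseline predictive), adjustment raised linear-model power from 0.08-0.34 to 0.16-0.50.

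**Step 3: what does the count distribution add?** One count per person, mean 5 drinks per week, rate ratio 0.5, t test against negative binomial (NB):

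| Per arm | Dispersion size, extra zeros | Null rejection, t / NB | Power at nominal 5%, t / NB | NB gain at equal true type I error |
|---|---|---|---|---|
| 30 | 0.5, none | 0.049 / 0.057 | 0.350 / 0.415 | +3.7 points |
| 30 | 1, none | 0.040 / 0.049 | 0.595 / 0.637 | +0.2 |
| 30 | 1, 30% | 0.045 / 0.031 | 0.378 / 0.344 | +5.5 |
| 18 | 0.5, none | 0.045 / 0.065 | 0.209 / 0.281 | +2.0 |
| 18 | 1, none | 0.047 / 0.058 | 0.388 / 0.456 | +2.5 |
| 18 | 1, 30% | 0.042 / 0.033 | 0.211 / 0.206 | +4.6 |

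Over all cells (rate ratios 0.4-0.6) the gain at equal true type I error was 0 to +7 points. With baseline adjustment in both models it was about -3 to +3 for quasi-Poisson and about -2 to +3 for a log-link model with HC3 errors.

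**Step 4: which standard errors?** Quasi-Poisson with model-based errors rejected 3.9-5.3% under the null in one set-up, but 6-15% in a second and 10-16% where baseline strongly predicted later drinking. HC3 errors gave 4.2-5.8%. A log-link arm-by-time test over three visits with ordinary robust errors gave 6.7-13.8%.

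**The case against.** Zeros and skew are inferred. The article states no distribution, the entry limits shorten the upper tail at baseline, and Data Analysis appears to set outlying values to missing, which would shorten it further. That stands: the shape is likely, not documented. Step 2 does not depend on it.

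The Abstract says outcome data will be assessed by linear and binomial regression, which could be read as a regression comparison of the arms. It names no covariate, however, and Data Analysis gives the intervention effect to the ANOVA.

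A reader might infer that the planned ANOVA gives false positives. The simulations do not support that.

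A reader might also infer that a count model would gain 5-11 points. That range does arise when baseline-adjusted quasi-Poisson is set against baseline-adjusted linear regression for a halved rate. But neither of those is the planned test, the gain was only 1-9 points when one arm had more abstinence, and model-based quasi-Poisson errors can be too small at this sample size. At equal true type I error the gain is near zero. Over three visits a log-link arm-by-time test gained 0 to +21 points after calibration. It replaces a difference of changes with a ratio of changes, so that does not isolate the distribution.

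Finally, the aim is similarity, not detection of a difference. That also stands: the small sample and the absent margin are larger causes of an uninformative result, and this change repairs neither.

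**Conclusion.** The point holds as one of efficiency, not validity. For a primary diary count the article fixes an unadjusted group-by-time ANOVA, although it collects baseline drinking that could be a covariate. For a halved drinking rate and 18-30 per arm, power is about 0.06-0.30 as planned, against about 0.11-0.57 with adjustment and a week-10 contrast. The sizes rest on assumed distributions and an assumed effect. The direction rests on the variance argument in step 2.

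The count distribution contributes about 0 points (about -3 to +7 for a single endpoint), so the case for a log link is interpretability and fit to a count, not power. Even after the change, power remains modest.

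**What to change.** Take daily drinking out of the ANOVA sentence in Data Analysis and state instead:

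- **Outcome:** diary drinks in a named week, week 10, with log of diary days completed as offset.
- **Model:** log-link mean model with arm and baseline drinks as covariates, the form of the baseline term fixed in advance.
- **Inference:** preferably a permutation test of the arm effect, otherwise small-sample robust (HC3) errors. Model-based quasi-Poisson errors should not be used.
- **Report:** the ratio of mean drinks with its 95% confidence interval, and the model-derived difference in drinks per day.

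The text should also say that genuine heavy-drinking days are not set to missing as outliers. Relapse stays in the ANOVA sentence and needs its own correction, because a yes/no outcome does not belong there.

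The cost is analysis wording and a check that the named software offers the chosen inference. No new data are needed. The headline effect becomes a ratio, and a few points of power may be lost (0-4 in simulation, against adjusted linear regression) if the arms differ only in a few heavy relapsers (10% against 35%).
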